**Table 3 T3:**
[figure not shown]
Parameters of the laser device in our study.

### Data collection

2.10

Personal information for each participant, including the written informed consent form, the FDI questionnaire, H-B S-B grading systems, and the S-B stiffness scale, will be managed by the research assistant and stored in a private place. All data will be scanned, converted into PDF files and stored in a USB drive with a valid password. Our study will not use the patient's name as a means of identification. The research assistant responsible for randomization will assign a study identification number to each participant. Confidentiality and privacy protection of the patient's personal information will be maintained throughout the entire clinical trial procedure. The data will be stored for 3 years after the study completion. While the study will be conducted, every 6 months an auditing trial conduct, which includes study procedure and data collection, will be executed by one of the research members who is not involved in treatment, assessment, or data analysis.

### Data monitoring

2.11

LAT represents a non-invasive method of treatment, thus, data monitoring committee (DMC) is not needed.

### Power analysis

2.12

The number of patients required for our pilot study is based on FDI data from a study in which the mean FDI score in the intervention group before the treatment was 68.6 with a standard deviation of 14.1, while the mean FDI score after the treatment was 80.7 with a standard deviation of 12.2.^[20]^ The sample size was based on a power of 80% (beta 0.2), statistical significance (alpha 0.05) of 95% (*P* = .05) and a dropout rate of 20%. Thus, this study will require 32 patients.

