### Primary outcome

2.6

The primary outcome measurement will be the change from baseline at 6 weeks in FDI scores on the social subscale.^[18]^ The FDI scoring system consists of 2 sections, a physical score, and social score. Each section consists of 5 multiple choice questions relating to either physical or social issues that occurred in the previous month. The FDI has shown good reliability and validity.^[18]^ FDI score evaluations will be performed on the first visit, the 9th and 18th visits, and will be compared with baseline scores. As far as we are aware, no traditional Chinese version of the FDI exists. We have therefore translated and proofread the English version into traditional Chinese.^[18]^

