## Discussion

3

We believe that this pilot study is the first-ever investigation into the use of LAT for the management of chronic Bell's palsy. Recent trials have described positive outcomes using acupuncture for chronic Bell's palsy^[8]^ and LLLT trials have shown good results in the treatment of acute Bell's palsy.^[13,14]^ This study aims to determine if LAT (delivered as gallium-aluminum-arsenide [GaAIA], infrared, 810 nm, 150 mw/cm^2^, 3/6 Joules per local/distal acupuncture point, applied for 40/80 seconds) improves physical and/or social functioning in patients experiencing inadequate recovery from chronic Bell's palsy.

In Asia, Bell's palsy is commonly treated with acupuncture in outpatient clinics.^[24]^ In a survey conducted in Taiwan from 2002 through 2011, the use of acupuncture for Diseases of the Nervous System and Sense Organs ranked fourth among adult patients.^[25]^ In 1996, the World Health Organization published a comprehensive review on acupuncture controlled clinical trials^[26]^ and outlined 64 symptoms treatable by acupuncture; Bell's palsy was included. However, all of the included clinical trials in that review focused on acute Bell's palsy. Clinical evidence is needed for the efficacy of acupuncture in chronic Bell's palsy.

LAT represents a non-invasive, pain-free method of treatment that has largely been investigated for its efficacy in the relief of pain-related conditions. Systematic reviews have discussed evidence in support of LAT.^[22,27]^ Importantly, when using laser acupuncture, the type of disease and laser parameters can greatly influence treatment outcomes,^[28]^ so must be taken into account; these variables include the wavelength, power output, and duration of irradiation. Notably, our study will differ from previous studies in that none of them used acupoints as target sites. We anticipate that our results will clarify how varying laser parameters may influence the clinical outcomes in the treatment of patients with the peripheral type of Bell's palsy. The results of this study are expected to indicate whether or not LAT is an effective therapy for patients experiencing inadequate recovery from Bell's palsy.

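### The stated 80% power and N=32 rest on one treated arm's before-after change and do not apply to the trial's real-versus-sham comparison

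*Protocol article*

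**What the plan says.** Section 2.12 (Power analysis) gives two inputs from the intervention group of an earlier study: "the mean FDI score in the intervention group before the treatment was 68.6 with a standard deviation of 14.1", and "the mean FDI score after the treatment was 80.7 with a standard deviation of 12.2". It then states "The sample size was based on a power of 80% (beta 0.2"), a significance level of 0.05 and "a dropout rate of 20%. Thus, this study will require 32 patients". It gives no response for a control group and no between-group difference, and does not say which FDI subscale the figures describe.

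The design is a comparison of two parallel arms, real and sham, with 16 randomised to each (Abstract, Methods; section 2.8). Section 2.6 fixes the endpoint: "The primary outcome measurement will be the change from baseline at 6 weeks in FDI scores on the social subscale". Section 2.13 plans paired and signed-rank tests within groups and a GEE model between groups. The Discussion says that the results are "expected to indicate whether or not LAT is an effective therapy".

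**The concern.** A before-after change in a treated arm is not a treatment effect. It also contains natural recovery, regression to the mean and placebo response, and a sham arm can show all three. Several features of this trial make some sham improvement plausible: entry requires FDI scores below 80, drugs and herbal medicines are unrestricted in both arms (section 2.4), and the sham device keeps its light and sound (section 2.2). Using the whole 12.1-point gain as the real-versus-sham difference assumes that sham does nothing.

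Readers will take the 80% as the chance of detecting a benefit over sham. If it is not, a non-significant result could be read as showing that LAT does not work when the trial had little chance of showing that it does.

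**Working it through.** **Inputs from section 2.12.** Before: 68.6 (SD 14.1). After: 80.7 (SD 12.2). Power 80%, alpha 0.05 (sidedness not stated), dropout 20%, N=32.

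**Assumptions made here.** Pre-post correlation r from 0.3 to 0.7; sham change of zero or, as an illustration, half of 12.1. The documents give neither.

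**Step 1: can 32 be reproduced?**
- Difference: 80.7 − 68.6 = 12.1.
- Pooled SD: √((14.1² + 12.2²)/2) = √(347.65/2) = 13.18.
- Standardised difference: 12.1/13.18 = 0.918.

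Power is from the noncentral t distribution with noncentrality difference/(SD × √(2/n)) and 2n − 2 degrees of freedom, n being the number per arm.

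| Route | Evaluable per arm | Total randomised |
|---|---|---|
| Two-sample, two-sided, 20% dropout | 20 (power 0.807; 19 gives 0.786) | 40/0.8 = 50 |
| Two-sample, one-sided, 20% dropout | 16 (power 0.814) | 32/0.8 = 40 |
| Two-sample, one-sided, no dropout | 16 | 32 |
| Paired within arm, two-sided, r=0.5, 20% dropout | 12 | 24/0.8 = 30 |
| Paired within arm, two-sided, r=0.45, 20% dropout | 13 (power 0.82) | 26/0.8 = 32.5, about 32 |

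A one-sided normal approximation using only the post-treatment SD of 12.2 also comes close: 13 per arm, and 26 × 1.2 = 31.2, rounded up to 32. No route found gives 32 as a two-sided between-group test with 20% dropout.

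**Step 2: power of the actual comparison.** Completers: 32 × 0.8 = 25.6, so about 13 per arm.
- SD of change: √(14.1² + 12.2² − 2r × 14.1 × 12.2).
- Residual SD after baseline adjustment: 12.2 × √(1 − r²), with 23 degrees of freedom.

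Example at r=0.5 on change scores: SD = √(347.65 − 172.02) = 13.25; standard error = 13.25 × √(2/13) = 5.20; noncentrality = 12.1/5.20 = 2.33; two-sided power 61%.

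| r | SD of change | Change score, sham unchanged | Adjusted, sham unchanged | Change score, sham improves by half (difference 6.05) | Adjusted, sham improves by half |
|---|---|---|---|---|---|
| 0.3 | 15.63 | 47% | 72% | 16% | 25% |
| 0.5 | 13.25 | 61% | 80% | 20% | 29% |
| 0.7 | 10.34 | 82% | 92% | 30% | 40% |

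Simulation of the baseline-adjusted analysis gave 70%, 79% and 91% with sham unchanged, and 23%, 28% and 37% with sham improving by half. The adjusted ranges are therefore stated as about 70-92% and 23-40%.

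**Step 3: precision at r=0.5.** The difference detectable with 80% power is 15.2 points on change scores and 12.1 with baseline adjustment. The 95% CI half-width for the difference in change is 2.064 × 5.20 = 10.7 points.

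**The case against.** The documents do not fix the true power. It depends on a correlation that they do not give and on how the GEE model handles baseline, which a condensed article need not spell out. A reader might infer that the trial simply lacks 80% power, or has about 60%. That goes too far: with baseline adjustment, r=0.5 and sham unchanged, power is about 80%, and on change scores it reaches 82% at r=0.7. This part of the objection stands, so the result has to be given as a range.

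Sham improving by half is an illustration and not a figure from the protocol. The Introduction also describes recovery as unlikely after 3 months and absent after 6, which limits natural recovery in patients enrolled at 3 months or later. That is fair, but it does not remove placebo response or regression to the mean.

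The number 32 may be sound arithmetic for a within-arm paired test with dropout, and section 2.13 does plan such tests. A reader might therefore call this a simple miscalculation, which the documents do not establish. The visible fault is that the inputs belong to a different comparison.

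Finally, this is a pilot with feasibility in its objective, and a pilot needs no power claim. But section 2.12 makes one, section 2.1 includes therapeutic efficacy in the primary objective, and the Discussion expects an efficacy answer. The label supports keeping N=32; it does not support keeping the 80%.

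**Conclusion.** The point holds in a conditional form. The stated 80% power and N=32 come from a single treated arm's before-after change on an unnamed FDI subscale, and do not apply to the between-group comparison on the social subscale. As a two-sided two-sample test, the quoted figures call for 50 randomised, not 32.

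With about 13 completers per arm, two-sided, r from 0.3 to 0.7 and no sham change at all, power is about 47-82% on change scores and 70-92% with baseline adjustment. The stated 80% can therefore be met, but only under the optimistic sham assumption together with a favourable correlation or baseline adjustment. If sham improves by half, power is 16-30% and 23-40%, and 80% is not reached. All of this takes the earlier study's means and SDs as valid for the social subscale, which section 2.12 does not say.

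At r=0.5 on change scores, a CI half-width of 10.7 points against a hoped-for 12.1 means that a non-significant result could not in general be read as evidence that LAT is ineffective.

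**What to change.** Keep N=32 and change two places.

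1. **Section 2.12.** Restate the calculation for real versus sham on change in the FDI social subscale at visit 18, with two-sided alpha and about 26 evaluable patients. State the sham change, the pre-post correlation and the analysis model as assumptions, and say which FDI subscale the source figures describe. Replace the 80% with the resulting range, or with the detectable difference: about 15 points on change scores or about 12 with baseline adjustment, at r=0.5.
2. **Discussion.** Reword the sentence on what the results will show, so that a non-significant result is reported as an estimated difference with its 95% CI and not as evidence that LAT is ineffective.

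The cost is the rewording. No patients, visits or procedures are added. The downside is that the power statement becomes conditional and less favourable than the present one.

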### Statistical analysis

2.13

Data analysis will be performed using SAS for Microsoft Windows, Version 9.4. The sample size and power calculations will be performed with G-power 3.0.10 for Microsoft Windows. Frequency and distribution will be assessed for categorical and numerical variable respectively. Wilcoxon signed rank test and Friedman test will be used to compare the FDI H-B, S-B scores and stiffness scale within each group as non-parametric analysis. Paired-T and ANCOVA will be used to compare the difference of correlated measurements within the subjects when distribution assumption fits. Generalized estimating equation (GEE) will be further applied to compare between measurements that will be taken at the first visit (baseline), after the 9th visit and 18th visit of the 2 groups and further multiple variable regression will be assessed in order to control the related risk factors.

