### Randomization and blinding

2.8

At visit 1, after undergoing screening for inclusion/exclusion criteria and baseline assessments, participants will be randomized to either the experimental (real LAT treatment) or the control (sham LAT treatment) group using a block randomization method^[21]^ and a randomization sequence created by Excel 2016 (Microsoft Office) before study commencement. The study groups will have 16 participants each. The balanced sample size will be ensured by dividing the subjects into even blocks of 2, 4, 6, or 8. Randomization will be conducted independently within each block; all 32 subjects will be divided into 4 blocks. For each block, 8 subjects will be randomly allocated into the intervention group or sham control group using a 1:1 ratio, irrespective of gender. Only the research assistant of this trial, who is responsible for this procedure and is not involved in the treatment, assessment, or data analysis, will know the randomization sequence. The participants, the investigators, the assessor, and the biostatistician will all be blinded to the allocation throughout the study period; the study researchers will remain blind to treatment allocation until the data are analyzed. participants will be allowed at any time point to withdraw from the study. In case that withdraw occurs and the participant will be interested to know group allocation; the study research assistant would provide the relevant information for the participant which include, participant's treatment assignment and outcome data.

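### The real-versus-sham comparison is left to a GEE over baseline and two later visits that is not tied to the week-6 primary endpoint, uses baseline inefficiently, and needs small-sample inference with 26 to 32 patients

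*Protocol article*

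**What the plan says.** The Primary outcome section fixes one endpoint and time point: "The primary outcome measurement will be the change from baseline at 6 weeks in FDI scores on the social subscale".

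The Statistical analysis section then names methods in three steps.

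- Rank tests: "Wilcoxon signed rank test and Friedman test will be used to compare the FDI H-B, S-B scores and stiffness scale within each group". These are within-group.
- Parametric tests: "Paired-T and ANCOVA will be used to compare the difference of correlated measurements within the subjects when distribution assumption fits". ANCOVA is named, but for within-subject comparison.
- GEE: "Generalized estimating equation (GEE) will be further applied to compare between measurements that will be taken at the first visit (baseline". Visits 9 and 18 complete the list, so baseline is one of three measurements compared. This is the only step that refers to both arms.

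An adjustment follows: "further multiple variable regression will be assessed in order to control the related risk factors". No factor is named and no number is set.

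On size, the Randomization and blinding section says "The study groups will have 16 participants each", and the Power analysis section allows for 20% dropout.

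**The concern.** In a sham-controlled trial the result that matters is the difference between arms. As worded, that difference comes only from the GEE, and the GEE sentence does not say which of its parameters answers the primary question. Three readings are open: a group effect averaged over visits, a joint group-by-visit test, or the group difference in change at visit 18. Only the last matches the stated primary outcome.

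Two further matters follow from the choice of method at this size. With baseline as a response, the visit-18 contrast is a comparison of change scores, which uses the baseline information less well than adjustment does. And the robust variance usually paired with GEE is too small when there are few independent subjects. At stake are precision that a trial of this size can ill afford, possibly a false-positive rate somewhat above the nominal level, and freedom to choose the contrast and covariates after seeing the data.

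**Working it through.** **Inputs.** From the article: 16 per arm, 32 in total, 20% dropout, alpha 0.05, three visits in the GEE. Expected completers: 32 × 0.8 = 25.6, about 26, or 13 per arm. The article gives no correlation between visits, variance estimator, test type or number of covariates. These are assumptions below. It also gives no operating characteristic for the GEE beyond alpha 0.05, so there is no figure of the plan's own to reproduce on this point.

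**1. Efficiency.** Assume equal SD σ at both visits and correlation ρ.

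- Change score: variance 2σ²(1 − ρ).
- Baseline-adjusted score: residual variance σ²(1 − ρ²).
- Ratio: 2(1 − ρ)/(1 − ρ²) = 2/(1 + ρ).

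| ρ (assumed) | Variance ratio | Interval width ratio (square root) | 16 per arm on change scores is worth this many per arm with adjustment |
|---|---|---|---|
| 0.3 | 2/1.3 = 1.54 | 1.24 | 16/1.54 = 10.4 |
| 0.5 | 2/1.5 = 1.33 | 1.15 | 16/1.33 = 12.0 |
| 0.7 | 2/1.7 = 1.18 | 1.08 | 16/1.18 = 13.6 |

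The single degree of freedom spent on the baseline covariate is ignored.

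**2. Type I error with an uncorrected robust Wald test, in closed form.** With complete data, n per arm and no covariates, the group-by-visit-18 contrast is the difference in mean change. Its sandwich variance is (n − 1)/n times the usual two-sample variance. Rejecting at |z| > 1.96 is therefore the same as rejecting at |t| > 1.96 × √((n − 1)/n) on 2n − 2 degrees of freedom.

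- n = 13: 1.96 × √(12/13) = 1.883 on 24 df, giving 7.2%.
- n = 16: 1.96 × √(15/16) = 1.898 on 30 df, giving 6.7%.

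For the joint two-df group-by-visit test the chi-square cut-off 5.991 converts to Hotelling's statistic, with F = 5.991 × (n − 1)/n × (2n − 3)/(2(2n − 2)).

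- n = 13: 5.991 × 12/13 × 23/48 = 2.650 on (2, 23) df, giving 9.2%.
- n = 16: 5.991 × 15/16 × 29/60 = 2.715 on (2, 29) df, giving 8.3%.

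**3. Simulation under the null** (5,000 to 8,000 trials per setting; 13 or 16 per arm; three visits; ρ = 0.5; exchangeable working correlation; 0, 3 or 5 null covariates). The first four rows use the uncorrected robust Wald test. The first range in each row is 13 per arm, the second 16 per arm.

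| Specification | Type I error |
|---|---|
| Baseline as response, week-6 contrast, 0 to 5 main-effect covariates | 6.4% to 7.5%; 6.3% to 7.0% |
| Same model, joint two-df test | 9.0% to 9.3%; 7.9% to 8.1% |
| Same model, week-6 contrast, 3 to 5 covariates each interacting with visit | 9.9% to 12.6%; 7.4% to 9.6% |
| Group effect averaged over visits, 0 to 5 covariates | 7.3% to 12.0%; 6.5% to 9.9% |
| Baseline as response, week-6 contrast, model-based SE (both sizes) | 4.4% to 5.8% |
| Same, Mancl-DeRouen sandwich with t reference (both sizes) | 2.9% to 4.4% |
| Week-6 ANCOVA with t reference (both sizes) | 4.2% to 5.6% |

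The model-based figure benefits from a working correlation that is correct in the simulation. A robust score test without covariates (20,000 trials) gave 5.3% for the visit-18 contrast at both sizes, and 4.9% and 5.0% for the joint test.

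If the GEE is moved to the post-baseline visits with baseline as a covariate, but the uncorrected Wald test is kept, the week-6 error is 7.6% to 11.4% at 13 per arm and 6.6% to 9.6% at 16. Baseline adjustment inside a GEE therefore needs the small-sample correction as well.

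**The case against.** The strongest reply is that the excess error is not a property of this plan. The article names no variance estimator, reference distribution, correction or covariate count. Those are commonly left to a SAP, which is not at hand, and several ordinary choices hold the level near 5%. That stands: the error figures can only be conditional, and their absence from the article is no fault in itself.

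Baseline as a response is also no error. The group-by-visit-18 contrast estimates the stated change from baseline without bias, so the objection to it is one of efficiency only. That stands too.

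ANCOVA is normally a between-group method, so the GEE may not be meant as the only comparison of arms. The sentence ties ANCOVA to within-subject differences, however, so under either intention the text needs rewording.

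Finally, this is a 32-patient pilot whose objective includes feasibility. True, but the same objective includes efficacy, and the article powers the trial for it.

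The reply does not reach two things: the named method is not connected to the article's own primary endpoint, and the adjustment set is open.

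**Conclusion.** The point holds in a limited form. As worded, the real-versus-sham comparison rests on a GEE over baseline, visit 9 and visit 18 in about 26 to 32 patients. It is not tied to the week-6 change in FDI social score, and an unlimited adjustment is added. The firm cost is efficiency: a variance 1.18 to 1.54 times that of baseline adjustment, for assumed correlations of 0.7 down to 0.3. The conditional cost is a type I error of about 6% to 7.5% for the week-6 contrast, or 8% to 9% for the joint test, if an uncorrected robust Wald test is used.

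Stronger readings that a reader might infer are not supported:

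- **An error rate of 10% or more as a feature of the plan.** That needs several covariates in other specifications (visit interactions, a visit-averaged effect, or baseline as a covariate with an uncorrected test). Main-effect covariates hardly move the week-6 contrast of the baseline-as-response model.
- **A halved treatment effect.** With linear growth to D, averaging over three visits gives (0 + 0.5D + D)/3 = 0.5D. The article does not state such a contrast, and its primary endpoint is week 6.
- **A recall-window defect.** The FDI items are described as "relating to either physical or social issues that occurred in the previous month", so at visit 9 (three weeks) about (30 − 21)/30 = 30% of the window precedes treatment. Visit 9 is not the primary time point, and at six weeks the window lies wholly within treatment.
- **Bias from dropout.** The 20% is a planning allowance, and no mechanism is stated that would make dropout depend on outcome.

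**What to change.** Reword the Statistical analysis section as follows.

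- State the primary analysis: real minus sham at visit 18 in the FDI social score, adjusted for baseline FDI social score. Use ANCOVA with a t reference, or a mixed model on visits 9 and 18 with group, visit, group-by-visit and baseline, and Kenward-Roger degrees of freedom.
- If GEE is kept, name the visit-18 contrast and use a bias-corrected sandwich (for example Mancl-DeRouen) with a t reference.
- Replace the open-ended regression by a short list of covariates fixed before unblinding.
- Say plainly which listed tests compare arms and which are within-group descriptions.

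The cost is wording only. The data are already planned and SAS 9.4, already named, can fit these models. Intervals may be slightly wider than with an uncorrected sandwich, partly offset by the gain from baseline adjustment.
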